## Abstract

**Background:**

Cardiovascular disease (CVD) is the leading cause of death and disability worldwide. Despite the widespread availability of evidence-based clinical guidelines and validated risk predication equations for prevention and management of CVD, their translation into routine practice is limited. We developed a multifaceted quality improvement intervention for CVD risk management which incorporates electronic decision support, patient risk communication tools, computerised audit and feedback tools, and monthly, peer-ranked performance feedback via a web portal. The intervention was implemented in a cluster randomised controlled trial in 60 primary healthcare services in Australia. Overall, there were improvements in risk factor recording and in prescribing of recommended treatments among under-treated individuals, but it is unclear how this intervention was used in practice and what factors promoted or hindered its use. This information is necessary to optimise intervention impact and maximally implement it in a post-trial context. In this study protocol, we outline our methods to conduct a theory-based, process evaluation of the intervention. Our aims are to understand how, why, and for whom the intervention produced the observed outcomes and to develop effective strategies for translation and dissemination.

**Methods/Design:**

We will conduct four discrete but inter-related studies taking a mixed methods approach. Our quantitative studies will examine (1) the longer term effectiveness of the intervention post-trial, (2) patient and health service level correlates with trial outcomes, and (3) the health economic impact of implementing the intervention at scale. The qualitative studies will (1) identify healthcare provider perspectives on implementation barriers and enablers and (2) use video ethnography and patient semi-structured interviews to understand how cardiovascular risk is communicated in the doctor/patient interaction both with and without the use of intervention. We will also assess the costs of implementing the intervention in Australian primary healthcare settings which will inform scale-up considerations.

**Discussion:**

This mixed methods evaluation will provide a detailed understanding of the process of implementing a quality improvement intervention and identify the factors that might influence scalability and sustainability.

**Trials registration:**

12611000478910.

## Background

### Cardiovascular disease burden

Non-communicable diseases (NCDs)—including cardiovascular diseases (CVD), cancers, respiratory diseases, and diabetes mellitus—are the leading cause of death worldwide [1,2]. It is predicted that by 2030, NCDs will account for 75% of all deaths with the largest proportion of deaths attributed to CVD [3]. Globally, approximately 17 million (30%) deaths per year and 151 million disability-adjusted life years (DALYs) are caused by CVD [4].

In Australia, CVD is responsible for 34% of deaths and 18% of the burden of disease and injury, making it the largest contributor to health system expenditure [5]. Aboriginal and Torres Strait Islander people experience a greater CVD burden than other Australians, and this is a major contributing factor to the 10-year gap in life expectancy [6,7]. The majority of CVD is caused by modifiable risk factors, which include blood pressure, lipids, diabetes, body mass index (BMI), tobacco smoking, alcohol use, unhealthy diet, physical inactivity, and psychosocial stress [8]. Recent modelling suggests that a 25% reduction in the prevalence of six NCD risk factors alone (tobacco, alcohol, salt, blood pressure, obesity, and glucose) could reduce global disease burden by 25% in the next 10 years [9].

### Evidence practice gaps

International clinical guidelines recommend that assessment for CVD prevention and management should be based on a combination of risk factors (the ‘absolute risk’ approach) rather than treating risk factors such as elevated blood pressure and cholesterol in isolation [10-13]. Absolute risk calculation estimates an individual’s risk of a CVD event over time based on modifiable and non-modifiable risk factors such as age and gender. This enables early identification, management, and primary prevention of CVD for individuals at high risk. In combination with well-established secondary prevention recommendations for people who have experienced a previous CVD event, the absolute risk approach offers considerable potential for reducing CVD burden [14].

Despite the widespread availability and consistency of these guidelines and the availability of validated risk prediction equations, there are large evidence practice gaps. Health professionals tend to use these guidelines and equations sporadically and inconsistently [15,16]. In the Australian context, studies have found that only 50% of adults attending primary healthcare have been screened for CVD risk in accordance with guideline recommendations, and only 40% of those identified as high risk have been prescribed recommended medications [17,18]. International studies have similarly demonstrated that a minority of people are being provided with appropriate screening measures and preventive treatments [19]. The majority of CVD events can potentially be averted with adequate implementation of established treatments and interventions that are effective, efficient, and universally accessible in Australian primary healthcare settings. Primary healthcare is the ‘front-line’ for effective prevention and management of the increasing burden of chronic diseases. With 88% of Australians visiting a general practitioner each year, the opportunities to improve primary and secondary prevention of CVD at this level are great [20].

### Knowledge translation strategies

Given the magnitude of these evidence practice gaps in CVD prevention, effective quality improvement (QI) innovations that support health services to improve their outcomes are urgently needed. QI is a multidimensional concept that focuses on improving the efficiency and process of a program, service, or organisation, resulting in improved health outcomes [21,22]. The Agency for Healthcare Research and Quality (AHRQ) has identified nine broad QI strategies to improve quality of care: *provider reminder systems, facilitated relay of clinical data to providers, audit and feedback, provider education, patient education, promotion of self-management, patient reminder systems, organisational change, and financial incentives, regulation, and policy* [23]. An increasingly important component of QI strategies is an adoption of health information technologies (HITs). Meaningful use of electronic health records (EHRs), computerised provider order entry systems, and electronic decision support (EDS) are increasingly recognised as key enablers to improvements in quality and delivery of healthcare [24]. However, the overall impact of computerised QI interventions to improve CVD burden has been limited, and effects on patient outcomes remain unclear [25-27].

Whilst QI strategies have been well characterised, there is relatively little knowledge translation research to help guide how these strategies can be optimally implemented into routine practice [28,29]. The Canadian Institute of Health Research defines knowledge translation as ‘*the exchange, synthesis and ethically sound application of knowledge—within a complex system of interactions among researchers and users—to accelerate the capture of the benefits of research for patients through improved health, more effective services and products and a strengthened health care system*’ [30]. Whilst it is critical that QI interventions are robustly assessed for effectiveness, equally important is a detailed understanding of how those QI interventions are implemented, using process and economic evaluations. This will allow a deeper understanding of how the intervention worked/did not work, in which contexts was it most effective/ineffective, and why. Given QI interventions are inevitably complex in nature, robust evaluation requires the use of multiple theories and frameworks to answer these questions. By using knowledge translation frameworks, we are able to better identify active ingredients of the intervention that change behaviour, causal mechanisms of change, effective modes of delivery, and the intended population or target [31]. This will enable promotion and integration of the interventions into clinical practice, health systems, and policy.

### The treatment of cardiovascular risk in primary care using electronic decision support (TORPEDO) study

There have been few randomised evaluations of QI interventions in the Australian primary healthcare setting. We designed a multifaceted QI intervention for CVD risk management in Australian primary healthcare. The intervention drew on two established QI mechanisms: 1) electronic decision support and 2) audit and feedback (summary of the clinical performance over a specified period of time) [32-37]. The intervention was evaluated in the TORPEDO study, a cluster-randomised controlled trial (cRCT) involving 60 health services. Details of the trial are published elsewhere [38]. In brief, the system was integrated with the healthcare provider’s EHRs, and included (1) a real-time decision support interface using an algorithm derived from several evidence based national guidelines (Figure 1); (2) a patient risk communication interface which included ‘what if scenarios’ to show the benefits from particular health risk factor improvement during a consultation (Figure 2); (3) an automated clinical audit tool for extraction of data and review of health service performance (Figure 3); and (4) a web portal where services can view peer-ranked performance over time (Figure 4). Healthcare providers could use the point-of-care tool as part of a routine clinical consultation. For the audit and feedback component, quality indicators were developed for patients who had visited the health service at least three times in the preceding 2 years and once in the preceding 6 months. The population studied was based on national guideline recommendations for CVD risk screening and included Aboriginal and Torres Strait Islander people over 35 years and all others over 45 years [38].

**Figure 1 Fig1:**
[figure not shown]
**Real-time decision support interface.**

**Figure 2 Fig2:**
[figure not shown]
**Patient-oriented risk communication interface.**

**Figure 3 Fig3:**
[figure not shown]
**Automated data extraction tool—sample health service performance on CVD risk factor screening.**

**Figure 4 Fig4:**
[figure not shown]
**Quality improvement portal.**

Data were collected for 38,725 people from the 60 health services. Overall, when compared with control, the intervention was associated with a 25% relative (10% absolute) improvement in CVD risk factor screening. Overall, there was no significant difference in the prescribing rates of recommended medicines to people at high CVD risk. The intervention was, however, strongly associated with improvements in the sub-group at high CVD risk that was not prescribed with recommended medicines at baseline. There were also improvements in intensification of existing, recommended medication regimens. There were modest improvements in attaining blood pressure targets but no differences in other clinical outcomes. The improvements in recommended prescriptions to high risk patients were not accompanied by increased prescribing rates for patients at low risk [39].

Although the intervention exhibited significant improvements in some outcomes, it remains unclear how this intervention was actually used in practice and what factors promoted and hindered its use. Answers to these questions are critical in order to inform future directions for its implementation and for implementation of similar interventions in other settings.

In this paper, we outline our protocol for a theory-based process evaluation of the TORPEDO intervention. The broad objectives are to understand how, why, and for whom the intervention produced the observed outcomes and to develop effective strategies for translation and dissemination. The evaluation will identify which intervention components promoted or had minimal impact at the provider, patient, and system levels and the mechanism of change. It will also identify the contextual influences on the delivery of the intervention and its outcomes. The specific objectives are the following:To understand whether intervention effects are sustained in a post-trial setting;To identify implementation barriers and enablers;To understand how CVD risk is communicated in the doctor/patient interaction both with and without the use of the intervention; andTo identify cost considerations for delivering the intervention at scale in the Australian primary healthcare system.

## Design and methods

Taking a mixed methods approach, we will conduct four discrete but inter-related studies to address our study objectives. Specifically, we will adopt an explanatory sequential design whereby the qualitative data analysis will be used to gain a better understanding of the quantitative findings [40].

### Logic model

Drawing on the RE-AIM framework, a logic model was developed to assist in the planning, conduct, and evaluation of the research components (Figure 5) [41-44]. The model assesses five dimensions of the intervention at different levels (individual, health service/clinic or organisation, and community/population): (1) participant *R*each; (2) *E*ffectiveness of the intervention; (3) *A*doption by the target health service; (4) *I*mplementation fidelity, costs, and adaptations made during delivery; and (5) *M*aintenance of intervention effects over time. The model identifies and describes inputs, activities, outputs, and outcomes of the intervention [45]. The four objectives have been mapped onto the relevant components of the RE-AIM framework.

**Figure 5 Fig5:**
[figure not shown]
**Logic model for TORPEDO process evaluation.**

The logic model will be underpinned by three theoretical perspectives—realist evaluation [46], the theoretical domain framework (TDF) [47,48], and normalisation process theory (NPT) [49,50].

### Realist evaluation

Realist evaluation seeks to answer the question *what works*, *for whom*, *and in what circumstances?* [46]. This is accomplished by identifying and understanding the underlying mechanisms by which the intervention succeeds or fails in varying contexts to produce the patterns of outcomes. Therefore, unpacking of the underlying generative mechanisms of the intervention and its effects is contingent on understanding the features of the context (i.e. roles and relationships of personnel at health services, IT infrastructure, economic conditions, demographic, motivation and skills of health professionals, etc.) [46,51,52].

### Theoretical domain framework

Successful implementation of evidence-based guidelines and QI interventions depends largely on changing the behaviour of healthcare professionals and patients, who are influenced by external (i.e. organisational, environmental, resources) and internal (i.e. motivation, capability) factors. TDF is a consensus of numerous behaviour change models and comprises 14 domains derived from psychological and organisational theory (knowledge, skills, social/professional role and identity, beliefs about capabilities, optimism, beliefs about consequences, reinforcement, intentions, goals, memory attention and decision process, environmental context and resources, social influences, emotion, and behavioural regulation) [47,48,53].

### Normalisation process theory

In order for healthcare innovation and technology to become routinely embedded in every day work, we need to understand how the innovation is integrated within the existing practices of a healthcare organisation. NPT assists in understanding how health professionals implement an intervention. NPT identified four main components: (1) coherence (sense making by participants), (2) cognitive participation (commitment and engagement by participants), (3) collective action (the work participants do to make the intervention function), and (4) reflexive monitoring (the degree to which participants reflect on or appraise the intervention [49,54,55].

### Study 1: Post-trial effectiveness of the intervention (objective 1)

#### Aim

To assess the effects of the intervention at one year following completion of the cRCT.

#### Methods

At the end of study follow-up visit for the TORPEDO study, all 60 health services have the option to either continue the use of the intervention or have the intervention implemented for use in the usual care health services for an additional 12 months. A post-trial clinical audit data extraction at minimum of 24 months from baseline will be conducted for the health services expressing interest to use the intervention. The objective of this study is to assess the impact of the use of the intervention over time on the two primary outcomes: (1) proportion of CVD risk factor screening and (2) proportion of appropriate medication prescription in the high risk individuals for the intervention arm and usual care arm at post-end of study following baseline.

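### Study 1 collects 24-month data only from services that opt in to the tool, so its estimate of sustained effect describes a self-selected group, although the aim carries no such limit

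*Protocol article*

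**What the plan says.** Objective 1, at the end of the Background, is "To understand whether intervention effects are sustained in a post-trial setting". The Aim of Study 1 is "To assess the effects of the intervention at one year following completion of the cRCT". Neither is confined to services that go on using the tool. The logic model also lists maintenance over time among its RE-AIM dimensions.

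The Methods of Study 1 describe the offer at the end-of-study visit: "all 60 health services have the option to either continue the use of the intervention or have the intervention implemented for use". For the control side this means to "have the intervention implemented for use in the usual care health services for an additional 12 months". The data source follows: "A post-trial clinical audit data extraction at minimum of 24 months from baseline", which "will be conducted for the health services expressing interest to use the intervention". Results on the two primary outcomes are still planned "for the intervention arm and usual care arm at post-end of study following baseline".

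The Analysis section of Study 1 gives a log-binomial model with intervention (yes or no), time (baseline, 12 and 24 months), their interaction and a random centre effect. The Discussion names two key limitations: data collection late in or after the trial, and the purely Australian setting.

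**The concern.** Which services supply 24-month data is decided by the services themselves, after randomisation and, in the intervention arm, after experience of the tool. A service that declines has no 24-month outcome under this plan. If willingness to continue is related to how well the tool worked locally, the 24-month terms of the model rest on services that differ systematically from the randomised 60.

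The article itself expects services to differ. The Discussion calls the intervention's success moderate and not uniform, and Study 3 plans to explain both use and non-use.

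At stake is the headline answer to objective 1. Study 3 draws on that result, and the programme is meant to inform scale-up. This is a choice of data source fixed in the article and not a detail that an analysis plan could settle later, because no analysis recovers outcomes that were never extracted.

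**Working it through.** The article gives no sample size, power or opt-in rate for Study 1, so there is no planned figure to reproduce. The check has two parts.

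**Aim against data.** The aim concerns effects after the trial, and the trial covered 60 services. The 24-month data cover only the services that express interest. The two coincide only if all services opt in, or if opting in is unrelated to the sustained effect.

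The random centre effect, read as a shift in a service's level, allows for services that are generally better or worse at screening or prescribing. It does not allow for services whose change over time is related to whether they opt in.

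**Illustration of direction (screening outcome only).** The Background reports a 25% relative and 10-point absolute improvement in screening. Together these imply:

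- control proportion = 0.10 / 0.25 = 0.40
- intervention proportion = 0.40 + 0.10 = 0.50
- risk ratio (RR) = 0.50 / 0.40 = 1.25

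The rest is assumed and not in the article: an opt-in share *p*, opt-in intervention services that keep the full +0.10, and other intervention services that keep *e* = 0 to 0.05.

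*(a) Maintenance within the intervention arm.* The RR over all intervention services is (0.40 + 0.10*p* + *e*(1 − *p*)) / 0.40. The extraction would show 1.25 in every row.

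| Opt-in share *p* | All-services RR, *e* = 0 | All-services RR, *e* = 0.05 |
|---|---|---|
| 40% | 0.44/0.40 = 1.10 | 0.47/0.40 = 1.175 |
| 60% | 0.46/0.40 = 1.15 | 0.48/0.40 = 1.20 |
| 80% | 0.48/0.40 = 1.20 | 0.49/0.40 = 1.225 |
| 100% | 1.25 | 1.25 |

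If the other services also keep +0.10, the all-services RR is 1.25 at any *p* and there is no bias.

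*(b) Contrast between arms at 24 months.* Suppose opted-in usual-care services gain *g* after receiving the tool. The RR between arms is 0.50 / (0.40 + *g*):

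- *g* = 0: 0.50/0.40 = 1.25
- *g* = 0.05: 0.50/0.45 = 1.11
- *g* = 0.10: 0.50/0.50 = 1.00

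At *g* = 0.10 the contrast is below every value in the table. At *g* = 0.05 it is below all of them except 1.10. So the planned contrast can fall on either side of the sustained effect over all services.

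The intervention term may instead mean current use. The 24-month extraction would then hold few or no non-using services, and the contrast could barely be estimated.

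**The case against.** Several points on the other side have force.

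- *The direction is not settled.* A reader might infer that the estimate must overstate the sustained effect. The Methods do not support that: opted-in usual-care services receive the tool, which pulls the contrast between arms towards no effect. This stands, and it limits the likely optimism to change within the intervention arm.
- *Services that later stop are not excluded.* A reader might infer that services which gave up the tool are removed. The criterion is interest expressed around the end-of-study visit, so a service that opts in and then lapses is still extracted. Only services that decline are lost.
- *Usual-care services cannot select on their own response,* since they had not yet had the tool. This also stands. Their interest may still mark services readier to change, but that is a different mechanism.
- *The Methods describe the objective as the effect of using the intervention over time,* which suits opt-in services better. A study of continuing services would be coherent, but the Aim and objective 1 are wider than that.
- *Non-use is examined in Study 3.* It is, in nine purposively chosen cases (six intervention, three usual care). These do not supply 24-month proportions for services that decline.
- *Covariates, counts by arm and opt-out comparisons are ordinary analysis-plan content.* Agreed. A reader might fault the model for its lack of covariates, but an article may leave these to a fuller document, and that is no part of this point.

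The article also does not say whether the baseline and 12-month records in the model come from all 60 services or only from those extracted at 24 months. Either way, the 24-month information comes from opt-in services alone.

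**Conclusion.** The point holds in a limited form. The aim is unrestricted, the 24-month data are restricted by a choice made after randomisation, the stated model does not deal with that selection, and the Discussion does not list it as a limitation. Followed as written, the plan would present a self-selected estimate as the sustained effect.

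For maintenance within the intervention arm, optimism is the likelier direction, on the assumption that services which decline retain less of the effect than those which continue. For the contrast between arms the direction is uncertain.

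The article does not allow the size to be calculated. In the illustration, an RR of 1.25 would be shown where the all-services value lies between 1.10 and 1.225 for opt-in of 40% to 80%. The gap disappears with complete opt-in or with equal retention in services that decline. Those inputs are assumed and concern screening only. Prescribing, the other primary outcome, showed no significant overall difference in the trial, and the illustration does not extend to it.

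**What to change.** **Preferred.** Run the 24-month de-identified extraction in all 60 services where participation agreements allow, whether or not they want the tool. Analyse by randomised arm, and describe post-trial use separately. The intervention term should be defined as randomised arm. Full extraction does not undo the uptake of the tool in usual care, so the 24-month contrast should be described as early against later access.

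**Where services are not extracted.**

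1. Report by arm the number of services offered the option, opting in and extracted.
2. Compare opt-in with opt-out services on baseline and 12-month outcomes.
3. Estimate the 12-to-24-month change only in services with data at both times.
4. Restrict the aim and conclusion of Study 1 to opt-in services.
5. Add this selection to the limitations in the Discussion.

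**Cost.** Extraction is automated and already runs in participating services, and Trial status says that quantitative analysis has not begun. The terms of the participation agreements are not shown and data collection is under way, so some agreement work may be needed. The fallback needs only existing data and wording. The price is that the sustained effect may look smaller or apply to fewer services.
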